### 9.2.3 Adverse Events:

Adverse events will be tabulated by body system using the COSTART dictionary, by severity, by seriousness, by relationship to study drug, and by elapsed time since last exposure to study drug. This yields primarily binary data (for each subject, the given COSTART event did or did not occur) which may be analyzed in the same manner as the binary reactogenicity events. Since multiple comparison corrections will not be used in this safety analysis, this analysis is vulnerable to grossly elevated type I error.

### 9.2.4 Vital Signs and Clinical Laboratory Measures:

Mean values for each measure will be plotted separately by treatment group, including ± one standard deviation. Extreme values and/or outliers will be discussed individually. For clinical laboratory measures within cross-over groups, quantitative outcomes at baseline and day 28 will be compared by paired Student’s t-tests and Wilcoxon signed rank tests. Binary outcomes will be compared by McNemar’s tests. This analysis is also vulnerable to elevated type I error.

## 9.3 Illness Definitions and Analysis for Challenge Component:

9.3.1 Fever:

Fever will be defined as any oral temperature 37.9C which is confirmed by a repeat observation at an interval of not less than 20 minutes and not more than 60 minutes. Prior experience has shown that electronic digital thermometers used in climate-controlled environments may not precisely reflect the normal oral temperature range established in the era of mercury bulb instruments used in ambient conditions. Accordingly, an alternative definition of fever, i.e., ≥ 3 standard deviations above the mean of the third temperature observation on **Challenge** Phase Day 1, will be utilized if significantly lower than 37.9º C.

9.3.2 Upper Respiratory Illness:

A subject will be considered to have upper respiratory illness if he or she has any one of the following on two (2) consecutive days, at least one (1) day of which must feature grade 2 severity, or if any of the following attain grade 3 severity once:

- Self-reported symptoms:
  - Rhinorrhea (runny nose), or
  - Nasal congestion (stuffy nose), or
  - Sore throat.
- Physician findings:
  - Nasal discharge
  - Otitis
  - Sinus tenderness
  - Pharyngitis

9.3.3 Lower Respiratory Illness:

A subject will be considered to have upper respiratory illness if he or she has any one of the following on two (2) consecutive days, at least one (1) day of which must attain grade 2 severity, or if any of the following attain grade 3 severity once:

- Self-reported symptoms:
  - Cough, or
- Physician findings:
  - New wheezing, rhonchi, râles, or signs of consolidation

9.3.4 Systemic Illness:

A subject will be considered to have upper respiratory illness if he or she has any one of the following on two (2) consecutive days, at least one (1) day of which must attain grade 2 severity, or if any of the following attain grade 3 severity once:

- Headache
- Myalgia and/or athralgia

9.3.5 Illness (Any):

A subject will be considered to have illness if he/she fulfills the criteria for fever, or upper respiratory illness, or lower respiratory illness, or systemic illness or any combination thereof.

9.3.6 Infection:

A subject will be deemed to be infected if he/she has any one of:

- Influenza virus shedding in nasal wash at any level, or
- Detection of influenza virus in the throat swab by using **culture, antigen detection or** molecular biology techniques, or
- A  4-fold increase in serum A/Panama/2007/99 HAI antibody titer between day 39 ( 3) and the final follow-up visit, and absent clinical disease suggesting influenza between discharge from the isolation unit and the final follow-up visit.

9.3.7 Laboratory-confirmed Influenza Illness:

A subject will be deemed to have laboratory-confirmed influenza illness if he/she meets the definitions for BOTH of:

- Influenza infection, and
- Illness (Any).

9.3.8 Analysis:

9.3.8.1 Power Considerations:

The analysis will consider both binary outcomes (e.g., illness vs. no illness; virus shedding vs. no virus shedding, etc.) and continuous outcomes (e.g., treatment group mean temperatures, tissue counts, peak viral shedding and shedding AUC, etc.). The variability, and potential magnitudes of the differences in the latter are *a priori* unknown. However, the virus challenge inoculum will be selected to yield *approximately* 50 - 60%, based on past experience, of the binary outcome “any illness.” (Closer control of this rate is difficult to ensure.) Assuming that a minimal efficacy level of 70% (where efficacy = [rate controls -ratetreated ] x 100 / rate controls) is of interest to justify further development of a given dose or formulation, it is possible to calculate that a group size of 28 will yield ≥ 0.80 power to detect a ≥ 70% reduction in the rate of the binary outcome “any illness.”

9.3.8.2 Analyses:

The analysis concerns between-group comparisons of the four cross-over groups regarding clinical and immunologic binary outcomes. Alternative definitions provide six binary clinical outcomes (fever, upper respiratory illness, lower respiratory illness, systemic illness, illness [any], and illness + infection) that can be compared between groups by chi-square tests. More flexible analyses use logistic regression (SAS PROC LOGISTIC) with the presence or absence of influenza, separately for each definition, as the outcome. Covariates are cross-over study group, age, gender, race, and, for some models, titers after vaccinations 1 and 2.

Additional secondary analyses will be based on tissue counts (and weights, if feasible) as a marker of illness severity, and on virus shedding assessed by two methods: peak and a time-weighted average calculated as a trapezoidal-rule AUC. For both peak and AUC, viral shedding is in units of log10 (titer). These continuous data will be compared between cross-over groups by Student’s t-tests and Wilcoxon tests and, in a more flexible analysis, by linear model adjusted for the demographic and clinical covariates cited above.

Finally, the three binary measures of influenza and the two viral load estimates (peak titer and AUC) will be assessed relative to the two immunologic measures, HAI reciprocal titer and nasal secretory IgA. For the binary measures, mean viral load (for each measure) is compared by t-tests between those with and without influenza (for each definition). For the two immunologic measures, the test of association with viral load will be based on Pearson correlations of log-titers.

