Safety and immunogenicity data continue to be analyzed, but are in general consistent with prior experience. Approximately 70% of both one- and two-dose vaccinees had signficant aserum HAI responses. A per-protocol analysis of the challenge study data revealed influenza-like illness in 66.7% of challenged placebo recipients, 62.5% of challenged one-dose recipients (6.3% efficacy), and 31.8% of challenged two-dose recipients (52.3% efficacy); yielding a chi2 p value of 0.041 for the 3 x 2 table and a p value of 0.021 for trend with number of vaccine doses. However, examination of the data has revealed that physician exam findings were non-contributory with one exception: pharyngitis; and that the definition of pharyngitis as applied by the study physicians led to fulfillment of the criteria for “illness” in a number of essentially asymptomatic subjects. In addition, the calibration of the disposable digital thermometers used to monitor temperature was questioned, as these yielded mean baseline temperatures just over 36ºC. Setting aside physician-observed pharyngitis and using a definition of fever based on the baseline mean + three standard deviations revealed a similar, but much stronger, efficacy trend in the data: 57.1% illness in placebo recipients; 45.8% illness in one-dose recipients (19.8% efficacy); and 4.5% illness (92.1% efficacy) in two-dose recipients (chi2 p value of 0.0007 for the 3 x 2 table and a p value of 0.0003 for trend with number of vaccine doses). An analysis based on laboratory-confirmed influenza illness (which requires illness and either isolation of influenza virus or a four-fold rise in reciprocal HAI titer across the challenge interval) demonstrates 65% efficacy in the one-dose group and 100% in the two-dose group. Because the sensitivity of influenza culture has proved poor for this strain however, this analysis remains preliminary pending data from molecular detection methods and immunoflouresence studies.

The current study is being undertaken to: a) confirm the efficacy of the two-dose regimen at a 30 μg dose level, b) re-examine the efficacy of the one-dose regimen at the 30 μg dose level with refined illness criteria, and c) examine the possible efficacy of a two-dose regimen at a 15 μg dose level, which is also highly immunogenic.

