### 7.3.3 Temperature Measurements During the Challenge Phase:

From Challenge Phase Day 1 to Day 9, oral temperature will be recorded at least four (4) times daily. Because these readings are critical to definitions of illness and to symptomatic and specific therapy criteria, temperatures of ≥ 37.6ºC must be confirmed by a repeat measurement not less than 20 minutes and not more than 60 minutes after the first reading. Subjects will be instructed not to eat or drink during the interval between the two measurements.

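### The alternative fever definition has no stated confirmation rule, and repeat readings are required only from 37.6ºC, so a lower cut-off would leave readings that cannot be confirmed

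*Protocol*

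**What the plan says.** Section 9.3.1 of the protocol gives two fever definitions. The main one is an oral temperature of 37.9ºC "which is confirmed by a repeat observation at an interval of not less than 20 minutes and not more than 60 minutes". The second is "an alternative definition of fever, i.e., ≥ 3 standard deviations above the mean of the third temperature observation on" Challenge Phase Day 1, which "will be utilized if significantly lower than 37.9º C". The sentence on the second definition does not mention a repeat reading.

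Section 7.3.3 decides which repeat readings are taken during the challenge: "temperatures of ≥ 37.6ºC must be confirmed by a repeat measurement not less than 20 minutes and not more than 60 minutes" after the first. It justifies this by the importance of these temperatures for the illness definitions and for the therapy criteria.

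The background (section 1.0) explains why an alternative exists. In the earlier challenge study the calibration of "the disposable digital thermometers used to monitor temperature was questioned, as these yielded mean baseline temperatures just over 36ºC". A fever rule of baseline mean plus three SDs was then used when those data were re-examined.

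Under section 9.3.5 fever alone makes a subject ill in Illness (Any). Section 9.3.8.1 states power of at least 0.80 for that outcome, with 28 per group, a 70% reduction, and a challenge dose chosen to give about 50 to 60% illness.

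**The concern.** The repeat trigger is fixed at 37.6ºC, while the alternative cut-off depends on the data. The two fit together only if the cut-off lands at 37.6ºC or above, a band of 0.3ºC below the main definition. The alternative applies only when it is clearly lower than 37.9ºC, so it may well fall beneath that band.

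Readings from the cut-off up to 37.6ºC would then have no required repeat. There are two ways to treat them, and the protocol does not choose:

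- **Confirmation not needed.** A single reading makes the subject febrile and therefore ill. Chance readings add false illness in every arm and dilute the observed efficacy.
- **Confirmation needed.** These readings can never qualify, because the repeat was not scheduled. The first reading must in effect reach 37.6ºC, whatever the Day 1 data say.

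This is a matter of data collection. A repeat not taken within 60 minutes cannot be supplied by a later analysis plan.

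**Working it through.** **1. The plan's own power figure.** Inputs from sections 9.0 and 9.3.8.1: n = 28 per group, two-sided 0.05, placebo rate p = 0.50 to 0.60, vaccine rate q = 0.3p.

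Power = Φ[(p − q − 1.96·SE0)/SE1], where SE0 = √(p̄(1 − p̄)·2/28), p̄ = (p + q)/2, and SE1 = √((p(1 − p) + q(1 − q))/28).

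At p = 0.50 and q = 0.15, p̄ = 0.325, SE0 = 0.1252 and SE1 = 0.1161. Power = Φ[(0.35 − 0.2453)/0.1161] = Φ(0.90) = 0.816. At 55% and 60% it is 0.873 and 0.919. The stated figure of at least 0.80 reproduces.

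**2. Where the alternative cut-off falls.** Cut-off = mean + 3·SD. It lies below 37.6ºC when SD < (37.6 − mean)/3. The protocol gives no SD, and its only baseline mean is the earlier study's value of just over 36ºC. The means and SDs below are therefore assumptions.

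| Mean (ºC) | Break-even SD (ºC) | Cut-off at SD 0.2 / 0.3 / 0.4 / 0.5 / 0.6 (ºC) |
|---|---|---|
| 36.0 | 0.53 | 36.6 / 36.9 / 37.2 / 37.5 / 37.8 |
| 36.1 | 0.50 | 36.7 / 37.0 / 37.3 / 37.6 / 37.9 |
| 36.2 | 0.47 | 36.8 / 37.1 / 37.4 / 37.7 / 38.0 |
| 36.6 | 0.33 | 37.2 / 37.5 / 37.8 / 38.1 / 38.4 |

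**3. False fever if single readings count (illustration).** Four readings a day on Challenge Phase Days 3 to 9 make 7 × 4 = 28. About two more on the afternoon of Day 2 give about 30. For a well subject with normally distributed readings, P(Z ≥ 3) = 0.00135 per reading.

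- Independent readings: 1 − (1 − 0.00135)^30 = 0.040.
- Readings sharing a subject effect, with within-subject correlation ρ: the average over b ~ N(0,1) of 1 − Φ((3 − √ρ·b)/√(1 − ρ))^30. This gives about 3.3% at ρ = 0.3, 2.6% at 0.5, and 1.6 to 1.7% at 0.7 (1.6% by simulation, 1.66% by numerical integration).

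This treats every reading beyond 3 SD as unconfirmed, which fits a cut-off well below 37.6ºC.

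**4. Effect on power.** A false fever adds illness only in subjects not otherwise ill, so each rate r becomes r + (1 − r)f. For example, with f = 0.04 the rates 0.50 and 0.15 become 0.520 and 0.184.

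| Placebo rate | f = 0 | f = 1.6% | f = 4.0% |
|---|---|---|---|
| 50% | 0.816 | 0.795 | 0.764 |
| 55% | 0.873 | 0.857 | 0.831 |
| 60% | 0.919 | 0.907 | 0.887 |

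**The case against.** The strongest reply is that this is a gap in wording with a small effect. The cut-off may not fall below 37.6ºC at all: at a mean of 36.6ºC the SD would have to be under 0.33ºC. The 4.0% figure is an upper value that needs independent readings. Power drops under 0.80 only at the bottom of the planned illness range. The illness-plus-infection outcome is better protected, because there a false fever counts only with evidence of infection. All of that stands, and it limits the size of the point. It does not settle what happens to readings between the cut-off and 37.6ºC.

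A reader might also infer several stronger things that the protocol does not support:

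- **That the thermometers are known to read low.** Section 1.0 says only that calibration was questioned in the earlier study, and nothing says the same devices are used here. A constant offset would in any case be absorbed by mean plus 3 SD.
- **That the cut-off will fall below 37.6ºC.** Without an SD this is conditional on the assumptions above.
- **That every fever under the alternative rests on one reading.** Readings of 37.6ºC or more are repeated under either definition, and the protocol is silent on confirmation; it does not waive it.
- **That false fever can be judged against the 4.5% illness rate in the earlier two-dose arm.** That rate was itself obtained with a mean plus 3 SD rule, so any false fevers are already in it.
- **That the cut-off can be tuned to the results.** Its value comes from Day 1, before inoculation on Day 2, and the trial is double-blind. What remains open is whether the alternative is used: "will be utilized if significantly lower than" 37.9ºC has neither a number nor a decision time. An analysis plan could supply the number, but it helps data collection only if fixed before challenge.

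**Conclusion.** The point holds as a mismatch between sections 9.3.1 and 7.3.3. The alternative definition has no stated confirmation rule, and the repeats that would confirm it are not required below 37.6ºC. The problem arises only if the alternative is used and its cut-off is under 37.6ºC. That follows if the baseline mean is again close to 36ºC and the SD is below about 0.5ºC, neither of which the protocol establishes for this trial.

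If single readings were counted, the illustrative cost is 1.6 to 4.0% false fever among well subjects. At the planned 28 per group, that is a loss of about 0.02 to 0.05 in power at a 50% placebo rate (0.816 to 0.795 or 0.764), with power still at least 0.83 at 55 to 60%. These figures assume normal readings, about 30 per subject, and a 70% true reduction. The effect is modest, but it touches the outcome on which the power statement rests and can be prevented only before the data are collected.

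**What to change.** - **Section 7.3.3:** compute the alternative cut-off from the Challenge Phase Day 1 readings and record it before inoculation. For endpoint purposes only, repeat any reading at or above the lower of 37.6ºC and that cut-off.
- **Section 9.3.1:** state that the alternative definition needs the same confirmation at 20 to 60 minutes as the main one.
- **Section 9.3.1:** fix before challenge, as a number of degrees, how far below 37.9ºC the cut-off must lie for the alternative to be used.

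The cost is a few extra thermometer readings in subjects already in quarantine, and a few sentences of text. The temperature rules for treatment and discharge are not affected.

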## 4.2 Inclusion Criteria:

To be eligible for study, each subject will fulfill all of the following criteria:

 Age 18 to 50 years, inclusive,

 Comprehension of the study requirements, including willingness to forego the licensed 2003-2004 intramuscular influenza vaccine until completion of study participation; availability for the required study period, ability to attend scheduled study visits, and willingness to participate in the inpatient challenge,

- Willingness to provide written consent for participation after reading the Consent Form and after having adequate opportunity to discuss the study with an investigator or qualified deputy,
- Good general health status as determined by a screening evaluation no greater than 90 days prior to the first immunization,
- For female subjects, provision of a history of reliable contraceptive practices (hysterectomy or bilateral tubal ligation, oral or implanted contraceptive use, intrauterine device, barrier method plus spermicide, history of a single male partner with vasectomy, or a history of abstinence deemed credible by the investigator). *The provision of this history does NOT replace the requirement to perform, and obtain negative results in, pregnancy tests as per sections 4.3 and 7.2.5.*
- Reciprocaltiter of serum hemagglutination-inhibiting (HAI) antibody to A/Panama/2007/99 (H3N2) ≤ 10.

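### Infection can be confirmed by a four-fold HAI rise from a baseline the vaccine has already raised, so efficacy on laboratory-confirmed illness can be biased upward by an unknown amount

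*Protocol*

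**What the plan says.** Protocol section 9.3.6 calls a subject infected if any one of three criteria is met:

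- virus in the nasal wash: "Influenza virus shedding in nasal wash at any level, or"
- virus in the throat swab: "Detection of influenza virus in the throat swab by using" culture, antigen or molecular methods
- serology: a "4-fold increase in serum A/Panama/2007/99 HAI antibody titer between day 39" (± 3) and the final follow-up visit, provided no influenza-like disease occurred after discharge.

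Section 9.3.7 builds an efficacy outcome on this: "A subject will be deemed to have laboratory-confirmed influenza illness if he/she meets the definitions for BOTH of" infection and any illness. Section 9.3.8.2 lists illness plus infection as one of six binary outcomes compared between groups.

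Section 4.2 admits only subjects with "antibody to A/Panama/2007/99 (H3N2) ≤ 10". A/Panama/2007/99 is one of the three vaccine strains (6.1) and also the challenge virus (6.7). On the previous challenge study, section 1.0 reports: "Approximately 70% of both one- and two-dose vaccinees had signficant aserum HAI responses". It adds a caution about its own confirmed-illness analysis: "Because the sensitivity of influenza culture has proved poor for this strain".

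**The concern.** The serological baseline is the Challenge Phase Day 0 sample, drawn after both test article doses. By then the arms differ by design: placebo subjects should still be near their entry titre, while many vaccinees will have risen against the very strain used for challenge. The criterion is a ratio to that baseline. A subject at 10 must reach 40; a subject at 40 must reach 160. If the larger absolute titre is harder to attain, the same infection is confirmed less often in an active arm than in placebo.

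Outcome misclassification would then depend on treatment, which pushes efficacy on laboratory-confirmed illness upward. In principle a vaccine that raised HAI without preventing influenza could show some efficacy on this outcome. Nothing in 9.3.8.2 repairs this. Post-vaccination titres enter as covariates only in some logistic models, and adjusting for a covariate does not correct a misclassified outcome.

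**Working it through.** **1. The protocol's own figures.** Section 9.3.8.1 claims at least 0.80 power for a 70% reduction in any illness with 28 per group and a placebo rate of 50-60%. The normal approximation gives 0.816 at 50% vs 15% and 0.919 at 60% vs 18%, so the figure reproduces. It does not involve infection status, so this point leaves it untouched.

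For the previous study, section 1.0 gives revised illness rates of 57.1% (placebo) and 45.8% (one dose). 1 − 45.8/57.1 = 19.8%, as stated.

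**2. Inputs for the bias.**

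- From the protocol: entry titre of 10 or less in all arms; a post-vaccination baseline; about 70% HAI responders in the previous study, which used 30 µg regimens; three criteria joined by OR.
- Not in the protocol, so assumed: s, the share of infections that show a four-fold rise (0.80 in placebo, 0.40 to 0.60 in vaccinees); v, the share detected by virus tests, taken as equal in all arms; independence of the two routes; perfect specificity.

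**3. Formula.** Combined sensitivity is v + (1 − v)s. With no true vaccine effect, apparent efficacy is

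1 − [v + (1 − v)s_vaccine] / [v + (1 − v)s_placebo].

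| v | placebo sensitivity | vaccine sensitivity, s = 0.60 / 0.40 | spurious efficacy |
| --- | --- | --- | --- |
| 0.5 | 0.90 | 0.80 / 0.70 | 11% / 22% |
| 0.7 | 0.94 | 0.88 / 0.82 | 6% / 13% |
| 0.9 | 0.98 | 0.96 / 0.94 | 2% / 4% |

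If s is the same in both arms, the bias is zero at every v.

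**4. Effect on the test.** Take 25 challenged per group (4.1), a true rate of 55% in both arms and s_vaccine = 0.40. An uncorrected Pearson test at two-sided 0.05 then rejects in 15% of trials at v = 0.5 and 7% at v = 0.9. Fisher's exact test rejects in 9% and 3.5%.

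**5. The previous study.** Its laboratory-confirmed analysis "demonstrates 65% efficacy in the one-dose group and 100% in the two-dose group", against 19.8% for one dose on revised illness. The rates fit 12/21 ill in placebo and 11/24 in the one-dose arm; these counts are back-calculated, not stated. Within the 12 and 11 ill subjects, 65% efficacy fits only two pairs of confirmed counts:

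- 5/21 vs 2/24: 1 − (2/24)/(5/21) = 0.65
- 10/21 vs 4/24: 1 − (4/24)/(10/21) = 0.65

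Either way, ill one-dose subjects were confirmed 0.44 times as often as ill placebo subjects: (2/11)/(5/12) = (4/11)/(10/12) = 0.44. Comparing those confirmation shares, Fisher's exact p is 0.37 for the first pair and 0.04 for the second. The protocol does not allow a choice between them.

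**The case against.** The strongest reply is that serology is only one of three routes. Nasal wash and throat swab are taken daily on Challenge Phase Days 3 to 9 (7.2.7), and antigen and molecular methods are allowed. With sensitive detection in everyone the bias is a few points. This stands as a limit on size. It does not remove the point, because 7.2.7 joins the methods with and/or, so no sensitive method is fixed for every subject.

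Second, an analysis free of serology is partly planned. Section 9.3.8.1 names shedding against no shedding as a binary outcome, and 9.3.8.2 compares peak and AUC shedding. This also stands. What is missing is illness confirmed by virus detection alone.

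Third, dropping serology would lose the most confirmed cases just where virus detection is weak, with about 25 challenged per arm. For that reason the composite should be kept and not replaced.

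A reader might also infer three stronger things that the protocol does not support:

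- *The move from 19.8% to 65% shows the bias at work.* Confirmation also removes illness not due to influenza, which raises efficacy in the same way. The protocol does not say which illness definition underlies the 65%.
- *Confirmation in the previous study leaned on HAI.* Culture is called insensitive, but no split between virus isolation and serology is given.
- *The choice among regimens would be misled.* Section 9.3.8.1 ties the 70% level that would justify further development to power for any illness, which serology does not touch. Five of the six listed binary outcomes do not use infection status, and section 9.0 says the trial is not meant to give definitive evidence of efficacy.

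**Conclusion.** The point holds as a possible upward bias in one of the six listed binary outcomes, laboratory-confirmed illness, and in infection itself. Its structure follows from the protocol: equal low entry titres, a vaccine containing the challenge strain, a baseline drawn after vaccination, and a ratio criterion that suffices alone.

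The step from a raised baseline to a lower chance of a four-fold rise is general reasoning about HAI, not a protocol figure. No Day 39 titre distribution is given, and by the 70% figure about 30% of vaccinees would not have responded. The direction is therefore plausible and the size unknown: 2% to 22% spurious efficacy over the assumed ranges, depending mainly on how sensitive virus detection turns out to be. Any illness and its power statement are unaffected. The previous study's results are compatible with this bias but do not demonstrate it.

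**What to change.** In 9.3.7 and 9.3.8.2, add a version of laboratory-confirmed illness in which infection means post-challenge virus detection in nasal wash or throat swab, with the same detection method applied to all subjects. Compare it between groups beside the composite that includes serology.

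Tabulate the cases confirmed by HAI rise only, by arm and by Challenge Phase Day 0 titre. State in advance that if the two versions disagree, efficacy on laboratory-confirmed illness will not be concluded from the composite alone.

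The daily washes and swabs and the Day 0 sera are already scheduled, so the cost is wording, one additional comparison and one table. The downside is fewer confirmed cases in the added version if detection is insensitive. That version removes only the serological part of the problem: if vaccination lowers shedding, detection can still differ by arm, though lower shedding may itself be a true vaccine effect.

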- Subjects who are afebrile (oral temperature < 37.9º C) and free of influenza-like illness symptoms of grade 2 severity, and have no ominous findings on their Challenge Phase Day 8 or 9 physical examination may be discharged with instructions to return to the clinic for the Challenge Phase Day 20 – 30 outpatient visit. Subjects will be supplied with sufficient oseltamivir or **amantidine** to complete their five-day regimen, and reminded to do so. Any subject who is either febrile (temperature > 37.9º C) or has persistent symptoms of grade 2 or greater (see diary card) will be retained in the facility for 24 hours additional observation and drug treatment unless the Investigator records a clear and compelling medical rationale for allowing discharge. Subjects who continue significantly symptomatic will be referred for appropriate medical care as needed.

7.1.15 Challenge Phase Day 20 – 30 (56 – 72 days after First Treatment; Final Follow-up Visit)

- Subjects will be queried regarding the occurrence of adverse events and any new concomitant medications taken, and the results recorded.
- A complete physical examination, including vital signs, will be performed and recorded.
- An ECG will be repeated if significant new abnormalities were noted prior to discharge from the quarantine facility.
- A nasal wash specimen for specific antibody assay will be obtained from each subject (see section 7.2).
- Subjects will provide a 15 mL sample of blood for HAI antibody testing (see section 7.2).
- This visit marks completion of protocol IDB-13005.

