## 7.4 Early Discontinuation:

Every reasonable effort should be made to ensure that each subject complies with the protocol and completes all study visits. However, a subject may withdraw or be withdrawn from participation if:

 The subject withdraws consent,

- The investigator recommends discontinuation in the interest of the subject’s safety or because of significant and irremediable protocol non-compliance,

 ID Biomedical, the ethics committee, or the MCA terminates the clinical trial.

Subjects must be stringently counseled that early withdrawal from the challenge isolation portion of the trial will be strongly discouraged, as it poses a risk both to the subject and to his/her contacts. Any subject insisting on early withdrawal during challenge isolation will be started immediately on a five (5) day course of oseltamivir (or amantidine), and will be encouraged to remain in the isolation unit as long as possible.

A complete Challenge Phase Day 20 – 30 (Final Follow-up Visit) evaluation and Study Termination case report form should be completed on any subject prematurely withdrawn from the clinical trial. No subject prematurely withdrawing/withdrawn will be replaced.

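### The serologic limb of Infection (9.3.6) is voided by any influenza-like disease after discharge, so a virus-negative seroconverter whose challenge illness continues is scored uninfected

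*Protocol*

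**What the plan says.** Section 9.3.6 gives three alternative routes to infection: "A subject will be deemed to be infected if he/she has any one of" the listed criteria.

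- Nasal wash: "Influenza virus shedding in nasal wash at any level, or".
- Throat swab: "Detection of influenza virus in the throat swab by using" culture, antigen or molecular methods.
- Serology: a 4-fold A/Panama HAI rise from day 39 (± 3) to the final visit, in a subject "absent clinical disease suggesting influenza between discharge from the isolation unit and the final follow-up visit".

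Only the serologic route carries a condition on what happens after discharge. Section 9.3.7 then builds on the result: "A subject will be deemed to have laboratory-confirmed influenza illness if he/she meets the definitions for BOTH of" influenza infection and Illness (Any). Section 9.3.8.2 lists illness plus infection as one of six binary clinical outcomes.

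The protocol expects some subjects to leave isolation with symptoms or ahead of time. Section 7.1.14 makes discharge depend on absence of fever and of grade 2 symptoms, so grade 1 symptoms do not prevent it. It allows exceptions on a recorded medical rationale, and adds: "Subjects who continue significantly symptomatic will be referred for appropriate medical care as needed". Section 7.4 covers early departure: "Any subject insisting on early withdrawal during challenge isolation will be started immediately on a five (5) day course of oseltamivir (or amantidine"), with the final-visit evaluation still to be completed.

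On the virologic routes, section 1.0 says of the previous challenge study: "Because the sensitivity of influenza culture has proved poor for this strain however, this analysis remains preliminary", pending molecular and immunofluorescence data.

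**The concern.** The protocol gives no reason for the condition. The plausible one is sound: influenza caught in the community after discharge should not be credited to the challenge. As worded, however, the condition asks only whether influenza-like disease was present after discharge, not when it began. Challenge illness that simply runs on disqualifies the serologic evidence as surely as a fresh infection does.

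The condition is also left without a grade, duration, onset or instrument. The symptom diary card ends on Challenge Phase Day 9, so two assessors could classify the same subject differently.

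At stake are the Infection outcome and laboratory-confirmed illness. An ill seroconverter can end up recorded as ill but not infected. Serology is a useful back-up here, because culture performed poorly for this strain and section 7.2.7 leaves the choice among culture, antigen and molecular detection open. Section 1.0 summarises the previous study's laboratory-confirmed illness as illness plus either virus isolation or a 4-fold HAI rise, and mentions no post-discharge condition. Since this trial sets out to confirm that study's two-dose result, any such condition should be deliberate and exact.

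**Working it through.** The plan states no figure on this point, so there is none to reproduce. The check is first logical, then illustrative.

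**1. The rule.** Infection = wash positive OR swab positive OR (4-fold rise AND no influenza-like disease after discharge). Laboratory-confirmed illness = Infection AND Illness (Any).

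**2. Who is affected** (all have a 4-fold rise and influenza-like disease after discharge):

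| Subject | Infection (9.3.6) | Laboratory-confirmed illness (9.3.7) |
|---|---|---|
| Completes isolation, any sample positive | Yes | Yes, if ill in isolation |
| Completes isolation, ill there, all samples negative, illness continues | No | No |
| Leaves early, samples taken so far negative, first ill at home | No | No, but the inpatient illness record is also largely missing |

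Wash and swab are taken daily on Challenge Phase Days 3 to 9 (7.2.7). A completer has 7 × 2 = 14 chances of a positive sample. A subject who leaves on Day 4 has at most 2 × 2 = 4, and so depends more on serology.

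**3. Share of cases lost.** Let s be the share of laboratory-confirmed cases detected by serology only, and q the share of those with influenza-like disease after discharge. The clause removes s × q of the cases. The protocol gives neither quantity. Assuming s = 10% to 50% and q = 5% to 30%:

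- lowest: 0.10 × 0.05 = 0.5%
- highest: 0.50 × 0.30 = 15%

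Take 25 per group (4.1), an assumed control rate of 55% for this outcome, true efficacy of 70% (active rate 0.55 × 0.30 = 16.5%), two-sided 0.05 and the normal approximation. Power with no loss is 0.832.

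| Loss | Equal share lost in both arms: power | Lost from controls only: power | Controls only: apparent efficacy, 1 − 0.30/(1 − loss) |
|---|---|---|---|
| 0.5% | 0.829 | 0.827 | 69.8% |
| 15% | 0.724 | 0.640 | 64.7% |

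Equal proportional loss leaves apparent efficacy at 70% and costs only power.

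**4. Sensitivity to single cases.** The counts are assumed: 25 per arm, starting from 12 placebo and 3 active cases. The test is two-sided Fisher, since section 9.0 says chi-square tests are exact. Efficacy = 1 − active/placebo.

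| Placebo v active cases | Cases lost | Efficacy | p |
|---|---|---|---|
| 12 v 3 | none | 75.0% | 0.012 |
| 11 v 3 | 1 placebo | 72.7% | 0.025 |
| 10 v 3 | 2 placebo | 70.0% | 0.051 |
| 11 v 2 | 1 placebo, 1 active | 81.8% | 0.008 |
| 10 v 2 | 2 placebo, 1 active | 80.0% | 0.018 |

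One or two reclassified subjects can move the result, and the direction depends on the arm that loses them.

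**The case against.** A reader might infer that everyone whose illness outlasts isolation is scored uninfected, or that the rule removes the longest and most severe cases. The text supports neither. The three routes are alternatives, and one positive wash or swab settles the matter whatever follows. Nothing in the protocol suggests that severe cases are the virus-negative ones.

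A reader might also infer that early leavers who fall ill at home are lost from laboratory-confirmed illness because of this clause. Mostly they are not. Illness (Any) rests on confirmed temperatures, diary grades and examinations collected in isolation, so such a subject largely lacks the illness record whatever 9.3.6 says. For them the clause matters chiefly to the Infection outcome.

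Further points limit the size. Section 5.2 calls challenge illness short lived and says confinement outlasts typical shedding. Febrile or grade 2 subjects are normally kept another 24 hours. The remark on culture concerns the previous study, and this protocol also provides for antigen and molecular detection, although its and/or wording does not commit to running them. It is arguable whether a residual grade 1 cough is clinical disease suggesting influenza at all.

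These points stand, and they narrow the finding to virus-negative seroconverters. They do not remove it. Nor is it a detail that can simply be left to an analysis plan: the protocol states a rule, and applied as written the rule misclassifies a kind of subject whom the protocol foresees.

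**Conclusion.** The concern holds in this limited form. A seroconverter who was ill in isolation, had no virus detected in any sample and remained symptomatic after discharge is scored uninfected and fails laboratory-confirmed influenza illness. An early leaver with few samples can be lost from the Infection outcome in the same way.

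The number of such subjects is probably small and cannot be estimated from the protocol; the 0.5% to 15% range rests wholly on assumed shares. It would be tempting to say that the clause biases efficacy towards no effect. That follows only if the affected cases are commoner on placebo. This is plausible if the vaccine shortens illness, but the documents do not establish it, and losing one case from each arm in the illustration raises apparent efficacy. The any-illness outcome used for the power statement in 9.3.8.1 does not use the infection definition and is untouched.

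**What to change.** Reword the third limb of 9.3.6 so that a 4-fold or greater HAI rise from Challenge Phase Day 0 to the final visit counts as infection unless a new influenza-like illness began after discharge. State that illness continuous with that recorded in isolation does not disqualify.

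Before unblinding, define how new and continuing illness are told apart, what counts as clinical disease suggesting influenza, and how subjects who leave isolation early are classified. At the Day 20–30 visit, record whether any post-discharge symptoms were new or continuing.

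The cost is one reworded sentence, a short written definition and one question at a visit that already asks about adverse events. The downside is small: a community infection that overlaps a lingering challenge illness would be counted as challenge infection. Settling the rule now also avoids a post hoc choice once the data are seen.
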